### Inclusion criteria

2.3

The proposed inclusion criteria are as follows: cases with moderate severity of COPD and moderate degree of air flow restriction according to GOLD guidelines (GOLD stages 2 and 3), adult patients aged 40 years or older at the time of obtaining consent. Any sex, outpatient cases, patients who, after receiving sufficient explanation before participation, have a thorough understanding of the study and provide written consent

### Exclusion criteria

2.4

The proposed exclusion criteria are as follows: patients who cannot breathe through the nose, patients with a history of pneumothorax, patients with active malignant tumor(s), patients with acute illnesses (e.g., acute myocardial infarction), patients currently diagnosed with asthma (patients with a history of asthma but currently diagnosed with COPD will be eligible for inclusion.), patients diagnosed with obstructive sleep apnea syndrome in the past, and patients diagnosed with obstructive sleep apnea syndrome in the past, or those with strong clinical suspicion of the condition, patients who are already using the NHF device, patients who are using NIV at night, patients with severe disease of the kidney, liver, or circulatory system, patients deemed unsuitable for the study by the investigator

### Study protocol

2.5

Evaluations will be performed during the 90 to 180 minute “daytime nap”^[13,14]^ in the measurement room of the Department of Anesthesiology and Biomedical Administration, Nagasaki University Hospital.

COPD patients, as an allocation factor, will be classified into 2 groups, a stage 2 group (80% ≧ FEV_1_ > 50%) and a stage 3 group (50% ≧ FEV_1_ > 30%), according to severity based on the standard FEV_1_.

#### Assessment of swallowing

2.5.1

Swallowing function will be examined by 3 tests: revised drinking test (Modified Water Swallowing test (MWST)), repeated saliva swallowing test (RSST), and cervical chest auscultation method (CCA). In addition, the hoop index will be calculated in all patients to evaluate the degree of postural change. In order to assess the correlation between swallowing of saliva during breathing and respiration, the rate at which the expiratory phase appears after swallowing will be analyzed from the respiratory curve, and the time of swallowing apnea will be measured.

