### Study design

2.1

The present study has been designed in accordance with the Standard Protocol Items: Recommendations for Interventional Trials and Consolidated Standard of Reporting Trials 2010 guidelines.^[11,12]^

This is an open-label, investigator-initiated, single center study on the efficacy of NHF therapy in COPD patients during the daytime nap as shown in Fig. 2.

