**Figure 2 F2:**
[figure not shown]
After obtaining informed consent, subjects who meet the registration requirements will be randomly assigned to either of the 2 groups. Fifty-percent of the patients will be randomly assigned to each group for this crossover study. The experimental group will be Oxygen therapy group with NHF application (40 L/m with air + 5 L O_2_ FiO_2_ = 0.3), control group will be Oxygen therapy group with nasal cannula (3 L/m oxygen FiO_2_ = 0.3).

The primary endpoint will be the occurrence rate of the expiratory phase after swallowing of saliva.

The Clinical Research Review Board of Nagasaki University has approved the study protocol. The study will be conducted at Nagasaki University Hospital in Japan. The study is registered in the jRCTs. The study will be conducted in accordance with the principles of the Declaration of Helsinki and the established best clinical practices of Japan. This is an exploratory study aimed at collecting information for conducting a verification study. Therefore, the number of cases will be set based on the feasibility in our hospital.

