#### Electromyography

2.5.2

An electromyogram (EMG) (manufactured by Bagnoli) will be used to measure muscle activity. The data measured by the EMG will be converted from an analog to digital signal (A/D conversion) at a sampling frequency of 1 kHz and loaded into a computer for analysis. Waveform analysis will be performed using myoelectric analysis software, and the bandpass filter will be set to 10 to 500 Hz. At the time of peak muscle activity, rest will be measured as 0 standard. The relative muscle activity will be calculated by normalizing the integrated value for 3 seconds during inspiration as 100% muscle activity

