#### Measurement of respiration

2.5.3

The coordination between swallowing and respiratory functions will be evaluated by a previously described method.^[13]^ Oxygen is administered through a nasal cannula in critically ill patients with COPD; therefore, respiration cannot be measured with a nasal flow sensor. Instead, an elastic band can be wrapped around the chest and abdomen, which can then be moved on the Impedance Plethysmograph, tracing the total movement of the chest and abdomen while swallowing. Apnea will be detected and lung parameters (lung volume) such as tidal volume, respiratory rate, and minute ventilation will be calculated. The starting time of swallowing will be recorded by the electromyogram. The starting time of swallowing will be recorded by the electromyogram. The transcutaneous CO_2_ concentration will be measured by attaching a TCO_2_ monitor (TCM5, manufactured by Radiometer, Japan, Tokyo) electrode to the earlobe, along with measurement of the transcutaneous oxygen saturation and pulse rate. The data will be stored in the internal memory of the device for subsequent retrieval and evaluation.

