### Outcome

2.7

The primary endpoint will be the frequency of swallowing of saliva during the measurement period and the rate of appearance of the expiratory phase.

The secondary endpoints will be: time-weighted average value of TcPO_2_ (average partial pressure during the observation period), time-weighted average value of TcPCO_2_ (average partial pressure during the observation period), time-weighted average value of SpO_2_ (average oxygen saturation during the observation period), time-weighted average respiratory rate (average respiratory rate during the observation period).

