### Data collection and management

2.10

The assignment and input tables to be used in this study will be created with the Research Electronic Data Capture (REDCap) software. The study will be conducted after the registered patients are allocated to groups and the data collected from the medical records are submitted to the researcher. A physician, co-doctor, and coworker will assign an ID to the medical records of each patient, which will be provided to the researcher. The Principal Investigator or Co-Researcher will approve the observation/inspection/evaluation data of each research subject immediately after confirming the content. The Principal Investigator and the Clinical Research Center Data Management staff will perform a visual and logical check of the data entered in the case report. The Principal Investigator or the Research Coordinator will be contacted in case of any discrepancies or queries regarding the data. The case will be fixed by performing data lock after resolving the issues and modifying the data (if indicated). The data management staff will be responsible for overseeing the process of correction of errors that arise after a case is locked. Proper conduct of the study will be monitored in accordance with the research plan.

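### No masked reading is provided for the traces that give the primary endpoint of this open-label crossover; coded scoring would be a cheap safeguard

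*Protocol article*

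**What the plan says.** Section 2.1 of the protocol article states: "This is an open-label, investigator-initiated, single center study". It makes no exception for outcome reading.

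The text below Figure 2 in the same section says: "The primary endpoint will be the occurrence rate of the expiratory phase after swallowing of saliva". Section 2.7 (Outcome) names two quantities: "The primary endpoint will be the frequency of swallowing of saliva during the measurement period and the rate of appearance of the expiratory phase".

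On measurement:
- **Phase (2.5.1):** "the rate at which the expiratory phase appears after swallowing will be analyzed from the respiratory curve". Section 2.5.3 explains that the curve comes from bands around the chest and abdomen, because a nasal flow sensor cannot be used with a cannula in place.
- **Swallow onset (2.5.3):** "The starting time of swallowing will be recorded by the electromyogram". Section 2.5.2 says the EMG signal is digitised and "loaded into a computer for analysis".
- **Method (2.5.3):** the evaluation of coordination follows a cited, previously published method, which is not reproduced.

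Section 2.10 says that records carry a patient ID and that the Principal Investigator or Co-Researcher "will approve the observation/inspection/evaluation data of each research subject immediately after confirming the content". It mentions no coding of condition or measurement day. No section names a trace reader or describes masked or independent reading.

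**The concern.** Two calls make up the primary endpoint: whether an event is a swallow, and whether the breath after it is expiratory. The swallow call sets swallowing frequency and the denominator of the phase rate. The phase call sets the numerator. Section 2.5.5 turns on whether a swallow falls in inspiration or at the change to expiration, around an apnea of less than one second. On a chest and abdomen movement trace recorded during a nap, some calls will plausibly be unclear.

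The article's rationale expects NHF to help. A reader who knows the condition may settle unclear calls in that direction without intending to. Each patient contributes one NHF and one control recording, so the within-patient comparison cancels stable patient differences but keeps an error that goes with the condition. The confidence interval would not reveal it.

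Section 2.11 uses the estimates to size the verification study. If that study is sized on an inflated difference, it will be too small.

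**Working it through.** The article states no figure to reproduce: the number of patients is set by feasibility, and no standard deviation (SD), reader agreement or share of unclear swallows is given. The check therefore has two parts.

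**1. The text.** The sections that could provide for masked reading are these:

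| Section | Content | Masking of the reader |
|---|---|---|
| 2.1 | open-label | none stated |
| 2.5.1, 2.5.3 | phase from curve, onset from EMG | reader not named |
| 2.5.2 | EMG digitised, software waveform analysis | not addressed |
| 2.5.5 | focus on swallowing and respiration | not addressed |
| 2.10 | patient ID, approval, checks, data lock | condition and day not coded |

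Masked reading is neither provided for nor ruled out.

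**2. Possible size (illustration).**

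From the article: n = 15 patients (2.2), each measured under both conditions (2.5.6), so 15 × 2 = 30 recordings; two-sided 95% confidence interval (2.11).

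Assumed: share of unclear swallows a = 10%, 20% or 30%; unclear swallows called expiratory with probability 0.75 under NHF and 0.50 under control; SD of the within-patient difference 10, 15 or 20 percentage points; no true effect.

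Spurious difference = a × (0.75 − 0.50):
- a = 0.10: 0.10 × 0.25 = 2.5 points
- a = 0.20: 0.20 × 0.25 = 5.0 points
- a = 0.30: 0.30 × 0.25 = 7.5 points

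Paired 95% half-width = t(0.975; 14) × SD / √15, with t = 2.145:
- SD 10: 2.145 × 10 / 3.873 = 5.5 points
- SD 15: 2.145 × 15 / 3.873 = 8.3 points
- SD 20: 2.145 × 20 / 3.873 = 11.1 points

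Chance that the interval excludes zero at SD 15 (normal approximation, standard error 15 / 3.873 = 3.87), against a nominal 5%:
- shift of 2.5 points: about 10%
- shift of 5 points: about 25%

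The ratio of shift to half-width runs from 2.5 / 11.1 = 0.23 to 7.5 / 5.5 = 1.4. The effect of biased swallow calls on frequency and on the denominator is not quantified.

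**The case against.** The strongest reply is that this rests on silence in a condensed article. Open-label describes the treatment session and does not settle who reads recorded signals afterwards. Reader procedures are often left to the full protocol, which may already provide for masked reading. The cited method may fix the swallow and phase criteria, and the EMG is processed by software, so the room for judgment is unknown. The study is exploratory, with 15 patients and no confirmatory claim.

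Much of this stands. A reader might infer from section 2.10 that the investigators score each session knowing the condition. The text does not support that. It describes sign-off of data per research subject, followed by checks, queries and data lock; it does not describe the scoring of traces, and approving entered data does not make the approver the reader. Nor does the article say that the reader is unmasked.

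Feasibility also has limits. Respiratory rate is itself a secondary endpoint, so NHF may show on the trace. Only digitisation of the EMG is documented; the sentence on internal device memory follows the transcutaneous monitor and does not show that the band trace is stored.

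What remains is that the article declares the study open-label without exception and sets out a data flow that codes the patient but not the condition. Followed as written, it permits reading with the condition known. Exploratory status lowers the weight, but the estimates still feed the next study's sample size.

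**Conclusion.** The point holds as a design weakness: no masked reading is provided for the traces behind either part of the primary endpoint. It does not establish that the reading will be unmasked or biased. The stronger claim, that investigators score the traces knowing the condition, goes beyond the documents.

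The possible shift of 2.5 to 7.5 points, against a half-width of 5.5 to 11.1 points, depends wholly on the assumed unclear share, reader lean and SD. If the calls turn out to be automated or fully rule-based, the shift could be close to zero. The article contains no wrong figure on this point and no contradiction. This is a cheap improvement.

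**What to change.** In sections 2.5.1 and 2.5.5, state that EMG and plethysmograph recordings are exported under random codes with patient, visit and condition removed; that existing study personnel score them in random order, for both swallow detection and phase, using the criteria of the cited method; and that the scores are locked before the code is linked. In section 2.10, state that investigator approval follows that lock for this endpoint. If the full protocol already provides for masked reading, one sentence saying so is enough.

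The cost is a coding step for about 30 recordings, which the existing data management staff could carry out, and it requires that the band trace be saved in exportable form. The sample size and treatment are unchanged. The downsides are that scoring is batched, so approval of this endpoint is no longer immediate, and that masking may be incomplete if NHF visibly changes the breathing pattern. Removing the explicit labels would still help.

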#### Electromyography

2.5.2

An electromyogram (EMG) (manufactured by Bagnoli) will be used to measure muscle activity. The data measured by the EMG will be converted from an analog to digital signal (A/D conversion) at a sampling frequency of 1 kHz and loaded into a computer for analysis. Waveform analysis will be performed using myoelectric analysis software, and the bandpass filter will be set to 10 to 500 Hz. At the time of peak muscle activity, rest will be measured as 0 standard. The relative muscle activity will be calculated by normalizing the integrated value for 3 seconds during inspiration as 100% muscle activity

#### Measurement of respiration

2.5.3

The coordination between swallowing and respiratory functions will be evaluated by a previously described method.^[13]^ Oxygen is administered through a nasal cannula in critically ill patients with COPD; therefore, respiration cannot be measured with a nasal flow sensor. Instead, an elastic band can be wrapped around the chest and abdomen, which can then be moved on the Impedance Plethysmograph, tracing the total movement of the chest and abdomen while swallowing. Apnea will be detected and lung parameters (lung volume) such as tidal volume, respiratory rate, and minute ventilation will be calculated. The starting time of swallowing will be recorded by the electromyogram. The starting time of swallowing will be recorded by the electromyogram. The transcutaneous CO_2_ concentration will be measured by attaching a TCO_2_ monitor (TCM5, manufactured by Radiometer, Japan, Tokyo) electrode to the earlobe, along with measurement of the transcutaneous oxygen saturation and pulse rate. The data will be stored in the internal memory of the device for subsequent retrieval and evaluation.

#### Sleep cycle analysis

2.5.4

The sleep cycle during naptime will be continuously monitored using a wristwatch type evaluator (Xiaomi Mi Smart Band4 activity meter). Body movements and breathing will be comprehensively evaluated by the device and each phase of nap sleep (non-REM, REM) will be measured. At the same time, an electrode of an electroencephalogram amplifier (GMS, MWM20) will be attached to the frontal region of the head for detailed evaluation of the sleep cycle.

#### Analysis of measurement data

2.5.5

Apnea of <1 second occurs during swallowing of saliva, which is a physiological characteristic, and functions to prevent aspiration by shifting to exhalation. However, aspiration may occur if a person swallows during the inspiratory phase instead of the inspiratory to expiratory transition phase. The analysis focuses on the interaction between swallowing function and respiration.

#### Measurement of the index of kyphosis

2.5.6

Curvature of the spine from the 7th cervical vertebra to the 4th lumbar spinous process will be considered for quantitative evaluation of kyphosis using an 80 cm long flexible curved ruler (made by Shinwa) in an easy sitting position with no plantar contact. The shape will be traced on the paper as a straight line L (cm) connecting the seventh cervical and the fourth lumbar spinous processes of the curve. The distance from the straight line L to the apex of the curve will be H (cm), based on the formula by Milne et al.^[14]^ The ratio will be calculated as the index of kyphosis.

We will administer NHF (30–40 L/min of air and 5 L of oxygen [FiO_2_ = 0.3]) during nap sleep, in order to assess the immediate effect of the therapy on swallowing function in patients with COPD. Assess swallowing function. On the first measurement day, patients will be randomly allocated to either the high-flow nasal cannula oxygen therapy group or the no NHF therapy group with only oxygen (3 L oxygen [FiO_2_ = 0.3]) group (1:1). The second crossover measurement will be performed at least 1 week after the first with reversal of treatments in the 2 groups. In both groups, oxygen will be administered by a nasal cannula at a flow rate sufficient to cause an increase in PaO_2_ to over 60 mm Hg (oxygen saturation >90%, usually ≤3 L/min at rest). Patients with hypercapnia due to COPD (arterial blood carbon dioxide partial pressure [PaCO2 ≧ 45 Torr]) in the stable period, history of exacerbation of COPD (moderate or higher) in the past year, and those requiring home oxygen therapy (COPD GOLD stages 2 and 3) will be the target cases.

### Adverse events

2.6

In this study, the NHF device will be secured onto the patient via a nasal cannula, and this could lead to discomfort. Moreover, an electrode for measurement of transcutaneous CO_2_ concentration will be attached to the anterior chest in both the NHF and non-NHF groups. This might cause temporary redness in patients with sensitive skin. Care will be taken to prevent undue harm to the patients in case of such adverse events.

### Outcome

2.7

The primary endpoint will be the frequency of swallowing of saliva during the measurement period and the rate of appearance of the expiratory phase.

The secondary endpoints will be: time-weighted average value of TcPO_2_ (average partial pressure during the observation period), time-weighted average value of TcPCO_2_ (average partial pressure during the observation period), time-weighted average value of SpO_2_ (average oxygen saturation during the observation period), time-weighted average respiratory rate (average respiratory rate during the observation period).

### Efficacy

2.8

We will evaluate the efficacy of the investigational device on a number of parameters, including the frequency of swallowing of saliva during the measurement period and the rate of appearance of the expiratory phase after swallowing.

Furthermore, we will evaluate other parameters such as time-weighted average value of TcPO_2_ (average partial pressure during the observation period), time-weighted average value of TcPCO_2_ (average partial pressure during the observation period), time-weighted average value of SpO_2_ (average oxygen saturation during the observation period), time-weighted average respiratory rate (average respiratory rate during the observation period).

### Safety

2.9

The proposed safety evaluation indices of this clinical trial are as follows: adverse events are any undesired or unintended signs (including abnormal laboratory values, abnormal vital signs), symptoms, or illnesses that occur between the onset of use of the NHF device and the end of the last observation. The causal relationship between use of the device and occurrence of adverse events will not be of significance to the study. Pre-existing symptoms and diseases will be treated as complications and not adverse events. However, if the complications worsen after use of the NHF device, they will be treated as adverse events, and the day of confirmation of the deterioration will be the date of occurrence of the adverse event.

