### Participant recruitment

2.2

Participants will be recruited from the Nagasaki University Hospital, where the subsequent study will also be conducted. The treating clinical research coordinator (CRC) will explain the study to the recruited individuals, and an informed consent form will be signed by those who agree to participate. This is a randomized crossover study, and will comprise 2 groups of patients. Both groups will be tested during the daytime nap, and the NHF device will be used concomitantly in 1 group.

After obtaining consent, subjects who meet the registration requirements will be randomly assigned to either of the 2 groups. Fifty-percent of the patients will be randomly assigned to each group for this crossover study as shown in the figure below.

Fifteen patients with stable COPD, aged 40 years or older, who need oxygen therapy and show FEV_1_% of <70% will be recruited from the Nagasaki University Hospital Respiratory Rehabilitation Center. Patients with hypercapnia due to COPD (arterial blood carbon dioxide partial pressure [PaCO2 ≧ 45 Torr]) in the stable period, history of exacerbation of COPD (moderate or higher) in the past year, and those requiring home oxygen therapy will also be recruited. Patients with hypercapnia due to COPD (arterial blood carbon dioxide partial pressure [PaCO2 ≧ 45 Torr]) in the stable period, history of exacerbation of COPD (moderate or higher) in the past year, and those requiring home oxygen therapy will also be recruited.

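### The adverse-event window in section 2.9 depends on randomised sequence: at least about 170 hours for NHF-first patients, but only the 1.5 to 3 hour NHF nap for control-first patients

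*Protocol article*

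**What the plan says.** Section 2.9 (Safety) fixes both edges of the adverse-event window: it takes in signs, symptoms or "illnesses that occur between the onset of use of the NHF device and the end of the last observation". Causal relation to the device plays no part in the definition. Conditions already present are classed as complications. They become adverse events only if they worsen after NHF use, dated to the day the deterioration is confirmed.

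The design comes from other sections. Section 2.2: "This is a randomized crossover study, and will comprise 2 groups of patients". Section 2.5.6: "On the first measurement day, patients will be randomly allocated to either the high-flow nasal cannula oxygen therapy group or the no NHF therapy group", in a 1:1 ratio, and then "The second crossover measurement will be performed at least 1 week after the first with reversal of treatments in the 2 groups". NHF is given "during nap sleep, in order to assess the immediate effect of the therapy on swallowing function in patients with COPD", so each patient has one NHF session. On session length, section 2.5 says "Evaluations will be performed during the 90 to 180 minute" daytime nap.

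The term that closes the window, the last observation, is not defined. Sections 2.7 and 2.8 use the related term for the recording made during the session, as in "time-weighted average respiratory rate (average respiratory rate during the observation period". The article describes no visit or call after the second measurement.

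**The concern.** A window that opens at first use of the device and closes at the end of observation suits a single-arm or parallel-group device study. In a crossover where half the patients receive the device last, the same wording gives two different windows, and randomisation decides which one a patient gets.

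Two things are at stake. First, the same NHF exposure is followed for a week or more in one sequence and not at all afterwards in the other. A respiratory deterioration confirmed the day after the NHF nap would count in an NHF-first patient and not in a control-first patient. Second, the control session lies inside the window in one sequence and outside it in the other, so there is no consistent control count to set beside the NHF count. Section 2.6 itself expects electrode-related skin reactions in both conditions: "This might cause temporary redness in patients with sensitive skin".

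The study is meant to inform a later verification study, so a safety count with this structure could be carried forward as if it described the device.

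**Working it through.** The plan gives no figure to reproduce here. The sample size rests on feasibility, and no safety rate is stated. The check builds the window for each sequence from the plan's own rules.

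**Inputs**
- Window: NHF onset to end of last observation (section 2.9).
- Interval between sessions: at least 1 week = 7 × 24 = 168 h (section 2.5.6). The text does not say whether this runs from the start or the end of session 1, so both are shown.
- Session length *s*: 90 to 180 min = 1.5 to 3 h (section 2.5).
- Patients: 15, allocated 1:1 (sections 2.2 and 2.5.6), taken as 7/8 or 8/7.
- Last observation: end of the second nap, because no later contact is described.

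**Window per patient**

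| Quantity | Formula | *s* = 1.5 h | *s* = 3 h |
|---|---|---|---|
| NHF-first, interval start to start | 168 + *s* | 169.5 h | 171 h |
| NHF-first, interval end to start | *s* + 168 + *s* | 171 h | 174 h |
| of which after NHF ends | 168, or 168 + *s* | 168 to 169.5 h | 168 to 171 h |
| Control-first | *s* | 1.5 h | 3 h |
| of which after NHF ends | 0 | 0 h | 0 h |

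All NHF-first figures are minima, because the interval is a minimum. On the shorter reading the ratio of windows is 169.5 / 1.5 = 113 or 171 / 3 = 57.

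**Share of adverse-event person-time from NHF-first patients (shorter reading)**
- *s* = 1.5 h, 7 NHF-first and 8 control-first: 7 × 169.5 = 1186.5 h against 8 × 1.5 = 12 h, so 1186.5 / 1198.5 = 99.0%.
- *s* = 1.5 h, 8 and 7: 1356 h against 10.5 h, so 99.2%.
- *s* = 3 h, 7 and 8: 1197 h against 24 h, so 98.0%.
- *s* = 3 h, 8 and 7: 1368 h against 21 h, so 98.5%.

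**What lies inside the window**

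| Segment | NHF-first | Control-first |
|---|---|---|
| NHF nap | inside | inside |
| Week after NHF | inside | outside (window closed) |
| Control nap | inside | outside (window not yet open) |
| Week after control | outside (window closed) | outside (window not yet open) |

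Only the NHF nap is covered in both sequences. The week after control is covered in neither.

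**Events lost.** If an event has probability *p* of appearing in the week after NHF, 15*p* are expected and 7*p* or 8*p* fall inside the window, a fraction of 7/15 = 47% or 8/15 = 53%. The documents give no value for *p*. Assuming 5% to 10% for scale only, 15 × 0.05 = 0.75 to 15 × 0.10 = 1.5 are expected and 7 × 0.05 = 0.35 to 8 × 0.10 = 0.8 are captured. The fraction lost follows from the 1:1 allocation and does not depend on *p*.

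**The case against.** The strongest objection is that the end of the last observation is undefined and the article condenses a full protocol that is not shown. A closing safety contact is the kind of detail an article leaves out. Section 2.9 mentions abnormal laboratory values although no laboratory test is described among the assessments, so there may be observations that the article does not list. This stands as a condition: the absence of follow-up after NHF in control-first patients is what the article's text yields, not an established fact about conduct. It does not remove the point. The window is stated explicitly, and its opening edge at NHF onset excludes the first-period control nap whatever happens later.

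A reader might infer that NHF will look safer than it is. The documents do not support a direction. Late events after NHF are missed in control-first patients. Against that, in NHF-first patients everything in the interval and the control nap is counted whatever its cause, while control-first patients contribute no control time at all. These features can pull in opposite directions.

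A reader might also infer that electrode redness would be missed because it is seen only when the sensor is removed. The article does not say when the sensor comes off, and section 2.9 defines events by when they occur, not by when they are noticed. Redness arising during a covered nap therefore counts.

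Finally, the exposure is one short nap, section 2.6 names only discomfort and temporary redness as risks, no endpoint is affected, and section 2.11 specifies no safety comparison between conditions. These facts stand and limit the severity.

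**Conclusion.** The point holds in this form: as written, what counts as an adverse event depends on randomised sequence. The window is at least about 170 h for NHF-first patients and 1.5 to 3 h for control-first patients, a ratio of at least about 57 to 113, with about 98% to 99% of adverse-event person-time coming from one sequence. Events in the week after NHF can be captured in 7 or 8 of the 15 patients, and control-session events in one sequence only. The resulting counts cannot be attributed to condition.

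This rests on two assumptions: that the second nap is the last observation, as the article's text implies, and that the 1:1 split is 7/8 or 8/7. The size and direction of any bias in a comparison between NHF and control are not determined. Severity is low to moderate: the rule is badly fixed for a crossover, but the study is exploratory and plans no comparative safety analysis.

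**What to change.** Rewrite the window in section 2.9 as follows.

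1. Open it at the start of the first session, whatever the treatment. Changing the closing edge alone would still leave the control-first patients' control nap uncovered.
2. Apply the same fixed length from the start of each session, in both sequences. The 1-week minimum interval already in the plan is one possible length, with a single telephone contact after session 2.
3. Tabulate events by the session and treatment they follow.

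If the full protocol already has a contact after session 2, name it as the closing edge; the opening edge still needs the change in item 1. If no later contact is added, make the change in item 1 and limit any comparison between conditions to in-session events, which can be observed equally in both sequences.

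The cost is a short rewording of section 2.9, about 15 telephone calls, and participation that ends about a week later for each patient. No endpoint, allocation or treatment procedure changes.
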